### Analysis methods

All analyses will account for clustering to ensure correct type I error rates and confidence intervals [13-15]. Many cluster randomised trials base their analysis on individual level patient data, and use appropriate statistical methods to account for clustering between patients in the same cluster (for example, mixed-effects models or generalised estimating equations). However, analysis methods based on individual level patient data may not perform well when the number of clusters is small [13,14]. Analysis for TRIGGER will, therefore, be performed using cluster-level summaries, which performs well even with a very small number of clusters [13,14].

Equal weight will be given to each of the six clusters. All analyses will compare the two treatment arms, unless otherwise stated. Binary outcomes will be presented as a difference in proportions.

### Unadjusted analyses

Unadjusted analyses using cluster-level summaries can be performed by calculating a summary outcome from each centre, and fitting a linear regression model with the summary outcome as a response variable, and treatment arm as a covariate. For example, for the outcome of mortality, one might choose the proportion of patients who died as a summary measure. To perform the analysis, one would then need to calculate the proportion of patients who died in each centre. A linear regression model would then be fitted, with the proportion of patients who died in each centre as the outcome, and which treatment the centre was randomised to as a covariate (in the TRIGGER trial there would only be six data points, as there are only six centres).

### Adjusted analyses

Adjusted analyses using cluster-level summaries will be performed as follows [14]:

1) A regression model (linear for continuous outcomes and logistic for binary outcomes) will be fit to individual-level patient data, and will be adjusted for the baseline characteristics listed earlier (age, shock, presence of coagulopathy and the number of major co-morbidities). The model will not adjust for treatment effect, or for centre.

2) Predicted values based on the fitted regression model will be calculated for each patient (for binary outcomes this equates to the predicted probability of experiencing an event, for continuous outcomes this equates to the predicted mean).

3) The expected outcome in each cluster will be calculated. For binary outcomes, this is the expected number of events in each cluster, and is calculated by summing the predicted probabilities for each patient in that cluster. For continuous outcomes, the expected mean value is calculated by taking the mean of the predicted values in each cluster.

4) An appropriate residual is calculated for each cluster. For binary outcomes, this is the observed number of events minus the expected number of events, divided by the number of patients in the cluster. For continuous outcomes, this is the observed mean minus the expected mean.

5) A linear regression model will be fit using the residuals calculated above as cluster-level summaries, with only the treatment group as a covariate. No degrees of freedom correction will be made for performing an adjusted analysis, as only patient-level variables will be adjusted for.

### Cluster level summaries for feasibility outcomes

Cluster-level summaries for feasibility outcomes will be calculated separately in each centre as follows:

1) **Recruitment rate (patients consenting):** the proportion of eligible patients providing consent.

2) **Ineligible due to severity of bleeding:** the proportion of screened patients who are ineligible due to severity of bleeding

3) **Overall adherence:** the mean adherence rate per patient

4) **Adherence per patient:** the proportion of patients who had no protocol deviations

5) **Adherence per Hb count:** the proportion of Hb counts that did not lead to a protocol deviation

6) **Selection bias - baseline variables for consented patients:** The mean age, baseline Hb, number of major co-morbidities, clinical Rockall score and Blatchford score, and the proportion of patients with shock will be calculated for consented patients.

7) **Selection bias - difference between consented and non-consented patients in baseline variables:** The difference in the mean Rockall score and Blatchford score, and mean baseline Hb between consented and non-consented patients will be calculated in each centre.

8) **Red blood cell exposure (number of transfusions):** the mean number of RBC units transfused per patient.

9) **Red blood cell exposure (patients receiving at least one transfusion):** the proportion of patients who receive at least one RBC transfusion.

10) **Hb concentration up to Day 7, and over the entire in-hospital follow-up period, prior to discharge/death/Day28:** the area-under-the-curve will be calculated for each patient

11) **Hb concentration at discharge:** the mean Hb will be calculated

### Cluster level summaries for clinical outcomes

The cluster-level summary will be calculated as the proportion of patients in each centre experiencing the event of interest for the following outcomes: further bleeding, all-cause mortality, need for therapeutic intervention at index endoscopy, need for surgery or radiological intervention to control bleeding, any thromboembolic or ischaemic events (and each of the components separately), acute transfusion reactions, infections and SAEs.

A cluster-level summary for length of hospital stay will be calculated using the median length of stay in each centre, and a cluster-level summary for health related quality of life will be calculated using the mean EQ-5D [16] in each centre.

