### Clinical outcomes

The clinical outcomes are:

• Further bleeding up to Day 28 (primary clinical outcome)

• Further bleeding up to hospital discharge

• All-cause mortality up to Day 28

• All-cause mortality up to hospital discharge

• Therapeutic intervention at the index endoscopy

• Surgical or radiological intervention to control bleeding up to death or discharge

• Occurrence of a thromboembolic or ischaemic event up to Day 28

• Occurrence of a thromboembolic or ischaemic event up to hospital discharge

• Acute transfusion reactions up to death or discharge

• Infection up to Day 28

• Infection up to hospital discharge

• Length of hospital stay

• Health related quality of life at Day 28

• Serious adverse events (SAEs) up to Day 28

The individual components that make up the composite outcome of a thromboembolic or ischaemic event (myocardial infarction, stroke, pulmonary embolus, deep vein thrombosis, and acute kidney injury) will also be analysed separately at both Day 28 and at hospital discharge.

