### Clinical outcomes

Main analysis of the clinical outcomes will be by ITT, and will include all consented patients with a recorded Hb below 12 g/dL during follow-up, and for whom the outcome is available. Including only patients with a Hb <12 g/dL allows us to target those patients most likely to be affected by the treatment policy, resulting in a more powerful analysis on a more relevant patient population. A Hb of 12 g/dL was chosen as the cut-off point because it is likely that some patients will be transfused (against policy) above 10 g/dL; if the proportion of patients transfused above 10 g/dL differs between treatment arms, excluding these patients could lead to bias. Using a cut-off of 12 g/dL should allow the majority of transfused patients to be included in the analysis, leading to an unbiased comparison. A secondary analysis will include all consented patients, regardless of whether their Hb dropped below 12 g/dL.

Results will be considered statistically significant at the 5% level. Main analyses for clinical outcomes will be unadjusted for baseline covariates; however, a set of secondary analyses will be adjusted for patient age, the presence of shock, the number of major co-morbidities, and the presence of coagulopathy (defined as an international normalised ratio (INR) >1.5 or a prothrombin time (PT) >3 seconds greater than the control). Mean imputation within the centre will be used for patients with missing baseline covariates [11]. Patient age and the number of major co-morbidities (encompassing ischaemic heart disease, cardiac failure, liver disease, renal disease, respiratory disease, malignancy and stroke) will be modelled using fractional polynomials to allow for the possibility of a non-linear association [12]. Further bleeding up to Day 28 is regarded as the primary clinical outcome.

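### Length of stay is compared by centre medians in the main analysis but by centre means in the adjusted one, so a difference between them does not show the effect of adjustment

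*SAP article*

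**What the plan says.** The SAP article lists "Length of hospital stay" among the clinical outcomes. Under Analysis principles, Clinical outcomes, it sets two layers of analysis: "Main analyses for clinical outcomes will be unadjusted for baseline covariates; however, a set of secondary analyses will be adjusted for patient age", with shock, co-morbidities and coagulopathy as the other covariates. Length of stay is not excepted.

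The unadjusted method (Unadjusted analyses) takes one summary per centre, "fitting a linear regression model with the summary outcome as a response variable, and treatment arm as a covariate". For this outcome the section Cluster level summaries for clinical outcomes names the summary: "A cluster-level summary for length of hospital stay will be calculated using the median length of stay in each centre". The same sentence gives EQ-5D a mean.

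The section Adjusted analyses has one route for binary and one for continuous outcomes. It begins: "A regression model (linear for continuous outcomes and logistic for binary outcomes) will be fit to individual-level patient data". For continuous outcomes, "the expected mean value is calculated by taking the mean of the predicted values in each cluster", and the centre residual follows: "For continuous outcomes, this is the observed mean minus the expected mean". These residuals are then regressed on arm. No median-based or log-scale route is given.

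**The concern.** An adjusted analysis placed beside an unadjusted one lets the reader judge whether baseline differences between arms explain the main result. With six randomised centres such differences are likely enough to make that a useful question. The comparison works only if covariate adjustment is the one thing that changes. For length of stay the summary changes as well, from median to mean. A shift between the two results could then be taken for the effect of baseline imbalance when part or all of it comes from the change of summary.

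There is a second, conditional consequence. If stay has a long right tail, a linear model on untransformed days is sensitive to a few long stays in a way that the median is not. An analyst who noticed the mismatch would have to devise an unplanned adjustment for medians, which works against the article's own case for fixing methods in advance.

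**Working it through.** The article gives no figure for length of stay, so there is nothing to reproduce. The check is a reading of the rules, then an illustration on assumed data.

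**1. What each rule estimates.** Remove all covariates, so that the adjusted procedure ought to return the main analysis.
- *Binary outcomes.* Every predicted probability equals the overall proportion p. The centre residual is (events − n·p)/n = centre proportion − p. The arm difference in residuals is the difference in average centre proportions, which is the main analysis.
- *EQ-5D.* Every predicted value is the overall mean. The residual is centre mean − overall mean. The arm difference is the difference in average centre means, again the main analysis.
- *Length of stay.* The residual is again centre mean − overall mean, so the arm difference is a difference in average centre means. The main analysis is a difference in average centre medians. The two do not agree even with nothing adjusted for.

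Length of stay is the only clinical outcome for which this happens.

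**2. Size for a uniform effect.** Assumption: lognormal stay, median 4 days, log-SD s. Mean = 4 × exp(s²/2). If every stay in one arm is 20% longer, the median difference is 0.2 × 4 = 0.80 days and the mean difference is 0.2 × mean.

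| s | Mean (days) | Mean/median | Median difference | Mean difference |
|---|---|---|---|---|
| 0.6 | 4.79 | 1.20 | 0.80 | 0.96 |
| 0.8 | 5.51 | 1.38 | 0.80 | 1.10 |
| 1.0 | 6.59 | 1.65 | 0.80 | 1.32 |
| 1.2 | 8.22 | 2.05 | 0.80 | 1.64 |

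For s from 0.8 to 1.2 the result in days grows about 1.4- to 2-fold with no imbalance in any covariate.

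**3. Weight of the tail.** Under the same model the longest 5% of stays hold 1 − Φ(1.645 − s) of all bed-days: 15% at s = 0.6 and 33% at s = 1.2. If 5% of one arm's patients, all already in the top tenth, stay 20 or 30 days longer, the median does not move. The mean rises by 0.05 × 20 = 1.0 or 0.05 × 30 = 1.5 days.

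**4. Both rules on the same simulated trials.** Assumptions: three centres per arm, 50, 100 or 150 patients per centre, s = 0.8 or 1.0, one weak baseline covariate, no between-centre variance, no treatment effect, 3,000 trials per setting. The two estimates correlated 0.47 to 0.59 and had opposite signs in 29% to 34% of trials. The SD of the mean-residual estimate was about 1.3 times (s = 0.8) to 1.7 times (s = 1.0) that of the median estimate. Summary and adjustment change together here, as they do in the plan, so these figures do not isolate the change of summary.

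**5. Can one hospital decide the result?** Three centres per arm, with "Equal weight will be given to each of the six clusters". Let one centre's residual differ by d and the other five be equal. Arm difference = d/3. Within-arm sum of squares = 2d²/3 on 4 degrees of freedom, so the pooled variance is d²/6. Standard error = √(d²/6 × (1/3 + 1/3)) = d/3. Hence t = 1 on 4 degrees of freedom, two-sided p about 0.37, whatever the size of d.

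**The case against.** The mismatch comes from reading several sections together. The adjusted section never names length of stay, its residual step speaks of choosing a suitable residual, and the article is a journal account of a longer plan. The sentence fixing the median is not confined to unadjusted analyses. The analyst may therefore have meant to carry the median through. That is possible, but the section goes on to define the residual for continuous outcomes, and the definition uses means. The point concerns a rule that is stated and does not fit one outcome, not detail left out.

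The illustration can also be faulted. The article gives no distribution of stay, and under the lognormal model the relative effect is 20% on both scales, so the growth appears only in days. Clear labelling would help a careful reader. All of this stands, and it limits what can be said about size. It does not remove the mismatch, because the plan's linear models report differences in days.

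A reader might infer more: that the adjusted result is driven by a few long stays, or that one hospital can decide it. The documents do not support either. They never state that stay is skewed; the median for stay against a mean for EQ-5D only suggests it. A single deviating centre among six raises the standard error along with the estimate, so it can move the estimate or mask an effect but cannot by itself produce significance at 5%. Sensitive to long stays, if skewed, is as far as the text allows.

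**Conclusion.** The point holds as an inconsistency between two stated rules. The main length-of-stay analysis estimates a difference in average centre medians, and the adjusted secondary analysis, followed as written, a difference in average centre means. That conclusion needs no assumption about the data, and it means that a gap between the two results cannot be read as the effect of covariate adjustment.

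The size does need assumptions. With lognormal stay, median 4 days and log-SD 0.8 to 1.2, the same 20% effect is 0.8 days on one scale and 1.1 to 1.6 days on the other. With little skew the gap would be small.

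The reach is narrow: one secondary analysis of one non-primary outcome in a feasibility trial. The median is a sound choice for the main length-of-stay analysis, and neither that result nor further bleeding to Day 28 is affected.

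**What to change.** Keep the centre median as the main analysis of length of stay. In the section Adjusted analyses, add a sentence for this outcome that gives the adjusted result an unadjusted counterpart on the same scale. Either of two forms would do:

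- **Median throughout.** Fit a median regression of stay on the listed covariates to patient-level data, without arm or centre. Take the centre median of the residuals as the cluster summary and regress it on arm. With no covariates this returns the main analysis exactly.
- **Log scale for the adjusted analysis.** Fit the linear model to log stay, with a stated rule for zero-day stays, and use centre mean residuals. Beside it, report the unadjusted comparison of centre means of log stay. Present both as ratios of geometric means.

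The cost is a different model for one outcome (first form) or one additional secondary estimate (second form). No new data are needed. Moving the main analysis itself to log stay would go further than the problem requires.

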### Subgroup analyses

Subgroup analyses will be performed for two outcomes: further bleeding and all-cause mortality (both up to Day 28) using an interaction test, and considered statistically significant at the 5% level. The following subgroup analyses will be performed:

• Variceal vs. non-variceal bleeding

• Ischaemic heart disease vs. no ischaemic heart disease

Interaction tests will be performed by calculating the difference in proportions (for the chosen outcome) between subgroups within each centre [14]. A linear regression model will then be fit, with the difference in proportions between subgroups as the outcome, and treatment as a covariate. Interaction tests will be unadjusted for baseline covariates, and will be reported with a 95% confidence interval.

### Sensitivity analyses

Missing data for each clinical outcome will be summarised by treatment arm. Sensitivity to missing data for further bleeding and all-cause mortality up to Day 28 will be assessed under a range of missing-not-at-random scenarios. This will be done by calculating the mean outcome in each cluster as follows:

$$\left(x_{\mathrm{obs}}\right)\left(1-p_{\mathrm{missing}}\right)+\left(x_{\mathrm{sensitivity}}\right)\left(p_{\mathrm{missing}}\right)$$

where *x*_*obs*_ is the observed cluster level summary, *p*_*missing*_ is the proportion of patients with missing data in that cluster, and *x*_*sensitivity*_ is the proportion of patients with missing data who are assumed to have had the event of interest. *x*_*sensitivity*_ will be varied between 0, 0.2, 0.4, 0.6, 0.8 and 1. The treatment effect and 95% confidence interval will be calculated as before.

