## Update

### Introduction

Acute Upper Gastrointestinal Bleeding (AUGIB) is the most common reason for emergency hospital admission with a gastrointestinal disorder in the United Kingdom (UK) with an annual incidence of 50 to 150/100,000 adults [1]. It is also the leading indication for red blood cell (RBC) transfusion, accounting for 14% of all RBCs transfused in England [2]. RBC transfusion is commonly based upon the patient’s haemoglobin (Hb) level; however, the optimal Hb threshold at which to transfuse is unclear [3,4]. Two observational studies have indicated an association between RBC transfusion after AUGIB and risk of further bleeding and mortality [5,6]. A recently published randomised trial found a liberal approach to transfusion led to an increased risk of mortality [7], although these results may not be generalisable due to the strict protocols of care implemented in this single centre trial, which are unlikely to be reproducible in most healthcare institutions.

The Transfusion in Gastrointestinal Bleeding (TRIGGER) trial is a cluster-randomised trial designed to evaluate the feasibility of implementing a restrictive *vs.* liberal RBC transfusion policy for patients admitted to hospital with AUGIB [8]. TRIGGER is a pragmatic trial which aims to reflect real world settings as closely as possible. Six hospitals in the United Kingdom were randomised in a 1:1 ratio to follow either a liberal transfusion policy (where eligible patients are transfused when their Hb drops below 10 g/dL) or a restrictive transfusion policy (where eligible patients are transfused when their Hb drops below 8 g/dL). Randomisation was performed using permuted blocks without stratification or matching, with a block size of six (to ensure three hospitals in each arm). Hospitals were randomised in July 2012, and recruitment took place between September 2012 and March 2013.

The TRIGGER protocol has been published in Transfusion Medicine Reviews [8] (available at http://www.tmreviews.com), and gives details on the rationale for the study, the inclusion/exclusion criteria, the sample size calculation and the process for consenting patients to the trial. This update to the published protocol describes the statistical analysis plan for TRIGGER.

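### The missing-outcome sensitivity analysis appears to assume one event proportion for missing patients in both arms, so it never examines missing patients faring differently between arms

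*SAP article*

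**What the plan says.** The Sensitivity analyses section states that sensitivity to missing data for two outcomes, further bleeding and all-cause mortality up to Day 28, "will be assessed under a range of missing-not-at-random scenarios". Each cluster summary becomes x_obs(1 - p_missing) + x_sensitivity × p_missing.

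The two quantities are described differently. p_missing is tied to the centre: it "is the proportion of patients with missing data in that cluster". x_sensitivity "is the proportion of patients with missing data who are assumed to have had the event of interest", with no mention of arm or centre, and a single list of values follows: it "will be varied between 0, 0.2, 0.4, 0.6, 0.8 and 1". Then: "The treatment effect and 95% confidence interval will be calculated as before".

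The analysis that is repeated is the cluster-level regression. Under Analysis methods, "Equal weight will be given to each of the six clusters". The Introduction describes randomisation "with a block size of six (to ensure three hospitals in each arm"), and Unadjusted analyses notes that "there would only be six data points, as there are only six centres". So each scenario is an equal-weight comparison of three values with three values, on 4 residual degrees of freedom.

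**The concern.** A treatment comparison is biased by missing outcomes mainly when the patients lost from one arm fare differently from those lost from the other. A sensitivity analysis labelled missing-not-at-random should include that case. With one x_sensitivity for both arms it does not: every scenario assumes that patients with missing outcomes have the same event proportion whichever policy their hospital followed. In effect, each scenario assumes no treatment difference among the missing, and only the common level is changed.

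At stake is how the check will be read for the primary clinical outcome and for mortality. If the arms lose similar proportions, six scenarios with the same point estimate could be taken as evidence of robustness when the estimate could not have moved.

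**Working it through.** **Inputs from the SAP article.** The substitution formula and the six values (Sensitivity analyses); equal weights (Analysis methods); three centres per arm (Introduction); regression on six values (Unadjusted analyses). The article gives no figure to reproduce here. It also gives no expected event rates and no expected missingness, so those below are assumptions chosen for illustration. Two-sided tests are assumed, in line with the 95% confidence intervals.

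**Algebra.** Write c for a common x_sensitivity, x_i and p_i for the observed proportion and missing proportion in centre i, and R and L for the restrictive and liberal arms. The substituted value is y_i = x_i(1 - p_i) + c·p_i, and the effect is

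mean_R[x(1 - p)] - mean_L[x(1 - p)] + c·(p̄_R - p̄_L).

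Three cases follow, whatever the event rates:

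1. Mean missingness equal between arms (p̄_R = p̄_L): the c term vanishes and the estimate is the same in all six scenarios.
2. Missingness equal to p in every centre: y_i = (1 - p)x_i + constant. Estimate and SE are both multiplied by (1 - p), so t and the p-value equal the complete-case ones at every c.
3. Missingness varying between centres or arms: the SE depends on c, or the estimate does, or both.

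**Complete-case illustration.** Assumed centre proportions are 4, 6, 8% (restrictive) and 12, 14, 19% (liberal).
- Difference: 6.0 - 15.0 = -9.0 points.
- Within-arm variances: 4 and 13 (points²); pooled (4 + 13)/2 = 8.5.
- SE = √(8.5 × 2/3) = 2.38; t = -9.0/2.38 = -3.78 on 4 df; p = 0.019.
- 95% CI: -9.0 ± 2.776 × 2.38 = -15.6 to -2.4.

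**Planned scheme, 10% missing in every centre.** Estimate 0.9 × (-9.0) = -8.1; SE 0.9 × 2.38 = 2.14; CI -14.0 to -2.2; t = -3.78; p = 0.019. All six values of c give this result. At 20% missing everywhere, all six give -7.2 points, p = 0.019.

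**Arm-specific values, equal missingness p in every centre.** The effect becomes (1 - p)(-9.0) + p(c_R - c_L) in points, with c_R and c_L as percentages; the SE is unchanged from the planned scheme.

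| Missing | c_R / c_L | Estimate (points) | p |
|---|---|---|---|
| 10% | any equal pair | -8.1 | 0.019 |
| 10% | 0.4 / 0 | -8.1 + 4.0 = -4.1 | 0.13 |
| 10% | 1 / 0 | -8.1 + 10.0 = +1.9 | 0.43 |
| 2% | 0.4 / 0 | -8.82 + 0.8 = -8.0 | 0.026 |
| 2% | 1 / 0 | -8.82 + 2.0 = -6.8 | 0.043 |

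**Planned scheme when missingness is not equal (same event rates, common c).**

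| Missing, restrictive v liberal | Estimate, c=0 to c=1 | p, c=0 to c=1 |
|---|---|---|
| 8/10/12% v 9/11/10% (mean 10% in each arm) | -8.1 throughout | 0.018 to 0.052 |
| 12% v 8% in all centres of the arm | -8.5 to -4.5 | 0.017 to 0.105 |
| 15% v 5% in all centres of the arm | -9.15 to +0.85 | 0.014 to 0.72 |

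In the first row the SE rises from 2.10 at c=0 to 2.97 at c=1, above the complete-case 2.38. The interval at c=1 is -16.4 to +0.1.

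**The case against.** The strongest reply is that the planned analysis is not inert. A reader might infer from the algebra that the six scenarios always coincide, or that the check cannot fail when missingness is merely similar. That is too strong. The p-value is fixed only if missingness is exactly equal in all six hospitals; with 8/10/12% v 9/11/10% the confidence interval crosses zero at c=1. With different loss by arm the estimate itself moves, and at 15% v 5% its sign changes. The plan also summarises missing data by arm, so readers will see whether this applies. All of that stands. It does not meet the point: the movement comes from unequal amounts of missing data, and no scenario lets the outcomes of missing patients differ between arms.

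A reader might also infer that substituting a fixed value always makes the interval too narrow. It narrows by (1 - p) when missingness is equal in every centre, but the first unequal case shows the SE rising above the complete-case value, so this is not a general defect.

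A common value in both arms is itself inferred from the missing index. The article neither states it nor rules out variation by arm, and the full plan is not shown. That is a fair limit on certainty. If arm-specific values were intended, however, the article does not say which combinations will be run, so the sentence needs completing either way.

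Finally, the practical size depends on how much is missing. At 2% even the 1 / 0 extreme leaves p below 0.05 in the illustration, and nothing in the article indicates that heavy loss is expected.

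**Conclusion.** The concern holds in a limited form. On the natural reading, the sensitivity analysis assumes the same event proportion for missing patients in both arms and omits the departure that most directly threatens the comparison. That the estimate is constant when arm-mean missingness is equal, and the p-value constant when missingness is equal in every centre, is algebra and rests on no assumed rates. The size is illustrative only: at 10% missing a 0.4 / 0 contrast halves the effect, from -8.1 to -4.1 points, while at 2% it moves it from -8.8 to -8.0.

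A reader might conclude that the plan will declare its results robust whatever the truth. The article does not support that: it commits to reporting effects and intervals, not to a robustness statement. The main estimate, test and analysis population are unaffected. As a sensitivity analysis in a feasibility trial, this should be corrected but falls below must-fix.

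**What to change.** In the Sensitivity analyses section, state that x_sensitivity is varied independently in the two arms over 0, 0.2, 0.4, 0.6, 0.8 and 1. This gives a 6 × 6 grid whose diagonal is the six scenarios already planned. Report the combinations at which the estimate changes sign or the 95% confidence interval crosses zero, beside the missing proportions by arm, and say that the extreme corners (0 in one arm, 1 in the other) are bounds and not plausible scenarios. The existing recalculation of the interval from the substituted centre values can stay.

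The cost is a sentence or two in the plan and, for each of the two outcomes, 36 runs of the same code instead of 6. No new data are needed.
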